### Design

This study uses a protocol for a randomized and controlled trial with blind evaluation.

### Setting

The study will be conducted in the general ICU of a tertiary level university hospital (Hospital das Clínicas at the University of São Paulo) in São Paulo, Brazil. The unit has a physiotherapist available at all times, and patients receive physical therapy twice a day. The patients receive respiratory care and mobilization from physical therapy professionals. There are no physiotherapy protocols in the unit; the protocol described in this article will be added to the physiotherapy routine for this research. The ICU is a general unit that receives patients with all kinds of illness as well as clinical and surgical patients. The average stay in the ICU is 12 days, and there are 14 beds.

### Participants

Participants will be patients admitted to the ICU who are 18 years old or older with a Barthel Index equal to 100 points before hospitalization, who have not been transferred from another hospital, and who meet the criteria for inclusion in the progressive mobilization program will be enrolled in the study. The criteria for for initiation and continuity the progressive mobilization program follow the safety consensus described in the academic literature [19] and some points are as follows: respiratory rate (RR) ≤ 35 breaths per min, absence of cardiac arrhythmias or acute ischemia, heart rate (HR) between 50 and 140 beats per min, without the use of vasoactive drugs or without dose increase, mean arterial pressure (MAP) between 60 and 120 mmHg, absence of active bleeding, and no prescription of bed rest. Patients with MV with inspired fraction of inspired oxygen (FiO_2_) ≤ 60% and positive end-expiratory pressure (PEEP) ≤ 10 cmH_2_O are also eligible to participate.

Patients to be excluded include patients with neurological diagnoses associated with motor alterations, who refuse to carry out the proposed exercises or ask to withdraw less than 3 days after beginning the protocol, with contraindications for movement, those with pre-existing amputations or who undergo amputation upon hospitalization, and those who die before the final evaluation will be excluded from the study.

After admission to the ICU, patients will be evaluated at all times of the day regarding the inclusion criteria in the program. Patients will be evaluated within 2 days of admission to the ICU to participate in the study. If they do not present the criteria for initiating a mobilization program in that period [19], they will not be randomized and will not be included in the study.

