### Details of the intervention and control

The study will consist of two groups: control and intervention. Patients will be randomized into groups using a computer program after evaluation of the inclusion criteria. Both groups will receive respiratory care according to the routine of the ICU and will receive physiotherapy twice daily. The ICU staffs a physiotherapist at all times. Patients in the intervention group will receive conventional physiotherapy in the morning and perform the research protocol in the afternoon period, thus receiving physiotherapy twice a day. Patients in the control group will also receive physiotherapy twice a day, performing conventional physiotherapy in both the morning and afternoon.

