**Fig. 1 Fig1:**
[figure not shown]
Progressive mobilization program

The patients will undergo the prescribed program therapy at the appropriate level for each patient, chosen based on the physiotherapist’s evaluation and evolving within the protocol as described below. The program should be started within 48 h of ICU admission. The patient will be included in the program throughout their stay in the ICU and will be assisted by a specific physiotherapist to apply only the prescribed protocol.

According to the program description (Fig. 1), the patients in the intervention group will have equipment and technologies for the therapy. These devices are a functional electrical stimulator (Fesmed II, Carci®, São Paulo, Brazil), dumbbells, shin guards, a Motomed Letto® active and passive cycle ergometer (RECK Company, Bremen, Germany), a fixed walker, a LiteGait 300MX-30® ambulatory device (Mobility Research, Tempe, AZ, USA), and a Wii Fit® video game with sitting and standing games (Nintendo®, Redmond, WA, USA).

If, during hospitalization, the patient evolves with criteria that indicate that any level of activity has been performed for more than 2 days, they will be excluded from the study.

The five levels of the early and progressive mobilization program (Fig. 1) are described below.

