#### Patient assessment procedures

At the time of admission to the ICU and up to 2 days after admission, the patient will be examined against the inclusion criteria. The patient’s functionality in the 2 weeks before admission will be evaluated with the Barthel Index, which will be assessed by directly questioning the patient or their caregiver if they are unable to respond. Evaluation will include hemodynamic, respiratory, and cardiac stability for the safe practice of early mobility, and the absence of exclusion criteria will also be assessed. The patient will then be randomly placed in the control group or the intervention group.

After the patient is enrolled in the study, the initial variables will be collected, consisting of data related to the patient and their hospitalized and pre-hospitalization levels of functionality. At that time, an accelerometer will be placed on the patient to monitor their level of physical activity during the entire stay in the ICU.

Data on the patient’s hospitalization and the evolution of their condition, as well as the level of physical activity performed, will be collected during the entire stay in the hospital.

Upon discharge from the ICU or within 2 days of discharge, all patients will undergo a complete evaluation of their respiratory, muscular, and functional systems through methods already described in the academic literature and performed by a blind evaluator. The accelerometer will be removed, and the data will be analyzed in a dedicated computer program. Figure 2 shows a flowchart presenting the methods used in the study.

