### Randomization procedures

Patients will be allocated to each group through computerized randomization. It will be a study of superiority, conducted in a single center. The patient allocation will be concealed, and the randomization of the individual will be performed by a researcher who is not involved in enrolling the participants, assigning them to groups, or performing follow-up measurements. This researcher will keep the allocation hidden in sealed brown envelopes within a box, which will be opened individually only at admission to the ICU when the participant is enrolled in the study. Individuals will be distributed between two groups. Only the researcher responsible for conducting the protocol will know how the participants are distributed.

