### Statistical analysis including sample size calculations

Analyses for all aims will be performed according to the intention-to-treat paradigm. Comparative analysis between the control group and the intervention group will be performed for all outcome variables. For the comparison of the physiological variables and the levels of activity between the groups, a statistical test will be used to compare the two independent groups. For parametric data, the *t* test will be used.

To calculate the sample size for the primary outcome, we based the design on results found in Schweickert (2009) for a clinical trial. To an estimated expected difference in means in the primary outcome (Barthel Index score) of 13 points and a standard deviation of 22 points. Considering a statistical power of 80% and an alpha error of 0.5, we found that the number of subjects should be 48 per group, totaling 96 patients in the study.

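### Exclusions that apply after randomisation, certainly death and early withdrawal, contradict the promised intention-to-treat analysis and can bias the primary comparison

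*Protocol article*

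**What the plan says.** All references are to the protocol article.

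- **Analysis principle** (Statistical analysis including sample size calculations): "Analyses for all aims will be performed according to the intention-to-treat paradigm". The Abstract also names intention-to-treat.
- **Exclusions** (Participants): "those who die before the final evaluation will be excluded from the study". The same sentence excludes patients "who refuse to carry out the proposed exercises or ask to withdraw less than 3 days after beginning the protocol" and "those with pre-existing amputations or who undergo amputation upon hospitalization".
- **A further exclusion** (Intervention group, text after Fig. 1): a patient whose course during hospitalisation indicates that "any level of activity has been performed for more than 2 days, they will be excluded from the study".
- **Timing of randomisation** (Details of the intervention and control): "Patients will be randomized into groups using a computer program after evaluation of the inclusion criteria". Under Randomization procedures, the envelope is "opened individually only at admission to the ICU when the participant is enrolled in the study".
- **Timing of the final evaluation** (Patient assessment procedures): "Upon discharge from the ICU or within 2 days of discharge, all patients will undergo a complete evaluation".

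The Participants section says separately that patients who do not meet the mobilisation criteria within 2 days of ICU admission are neither randomised nor included. So the article does distinguish patients who are never randomised from patients excluded from the study.

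**The concern.** Intention-to-treat keeps every randomised patient in the arm assigned. A rule that removes patients for what happens after allocation does the opposite, and it decides who enters the primary analysis. The groups compared are then no longer the groups that randomisation made alike.

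Two mechanisms are at stake. Patients who drop out early may have a different prognosis from those who stay. If more of them, or a different kind, leave one arm, its mean Barthel and IMS scores move with no treatment effect. Leaving out deaths restricts function at ICU discharge and ICU length of stay to survivors, a group that treatment may itself shape.

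Differential exclusion is plausible here. Only the evaluator is blinded, not the patients or therapists. Beginning the protocol is also wording that fits the intervention arm more naturally, since control therapy has no pre-established routine.

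**Working it through.** **1. Which exclusions fall after randomisation?** The order is: eligibility check (up to 2 days after ICU admission), randomisation, therapy, final evaluation at or within 2 days of ICU discharge. The unit's average ICU stay is 12 days (Setting).

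| Exclusion | After randomisation? |
|---|---|
| Death before the final evaluation | Yes, for any enrolled patient |
| Request to withdraw less than 3 days after beginning the protocol | Yes |
| Refusal of the proposed exercises | Possibly; it can also occur at consent or screening |
| Amputation during the hospital stay | Possibly; it can also precede randomisation |
| Activity-level criterion met during hospitalisation | Yes as placed, though its wording is unclear |

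Nothing in the article reconciles these rules with intention-to-treat or says how an excluded patient enters the analysis.

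**2. The plan's own figure.** Inputs from the Statistical analysis section: difference 13, SD 22, power 80%, 48 per group. Alpha is printed as 0.5; 0.05 two-sided is assumed, because 0.5 two-sided would need only 14 per group.

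- Normal formula: n = 2 × [22 × (1.96 + 0.842) / 13]² = 44.96, so 45 per group.
- Exact t test: 45.94, so 46 per group.
- With 48 evaluable per group, t-test power is 81.7%.

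The stated 48 is therefore 2 per group above the bare t-test requirement, and no allowance for exclusions is stated. If both arms lose 5%, 45.6 per arm remain and power is 79.7%. If both lose 10%, 43.2 remain and power is 77.5%.

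**3. Illustration of bias.** Assumptions, none of them from the article: normal scores, no true effect, exclusions in one arm only, a fraction p of that arm removed, and correlation r between being excluded and a poor score. The mean of those who remain rises by

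shift = r × SD × φ(z_p) / (1 − p), where z_p is the normal quantile at p.

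- p = 5%: φ = 0.1031, and 22 × 0.1031 / 0.95 = 2.39. Shift is 1.2 points at r = 0.5 and 2.4 at r = 1.0.
- p = 10%: φ = 0.1755, and 22 × 0.1755 / 0.90 = 4.29. Shift is 2.1 points at r = 0.5 and 4.3 at r = 1.0.

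Simulating 8,000 trials per setting with 48 per arm, the two-sided 5% t test rejects in 5.5% to 7.6% of trials at 5% loss, and in 8% to 16% at 10% loss.

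If both arms lose patients, only the contrast matters. With 10% against 20% lost, the shift is 7.70 − 4.29 = 3.4 points at r = 1.0 (1.7 at r = 0.5), in favour of the arm losing more. Equal rates with equal selection give zero.

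**4. Power if deaths are ranked worst.** Assumed: 48 per arm, difference 13 and SD 22 among survivors, death independent of the score, Mann-Whitney test at two-sided 0.05, 6,000 trials per setting.

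| Deaths, both arms | Power |
|---|---|
| 0% | about 80% |
| 10% | about 61% |
| 15% | about 51% |
| 20% | about 42% |

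**The case against.** The best defence is that patients who die have no Barthel or IMS score at ICU discharge, so some rule is unavoidable, and an article may leave its details to an analysis plan. The first half stands: a strategy for deaths is needed, and more than one is legitimate. The second does not remove the problem. The article does more than omit detail: it states a rule that removes randomised patients and, elsewhere, a principle that forbids this.

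Several stronger readings are tempting but not supported:

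- **That every listed exclusion is post-randomisation.** This is certain in the Participants list only for death of an enrolled patient and early withdrawal. Withdrawal at 3 days or later is not covered by that rule.
- **That the refusal and withdrawal rules act only in the intervention arm.** Controls also exercise, and the article uses the word protocol both for the whole study and for the intervention programme. A heavier effect on the intervention arm is an inference.
- **That refusers are the frailest.** Unresponsive patients enter at level I with passive therapy and cannot themselves refuse, so refusers may be mainly awake patients. The correlation of 0.5 to 1.0 is assumed; 1.0 means that exactly the worst patients leave.
- **That the comparison is biased in a known direction.** Early refusal could favour the intervention. A survival benefit could work against it, by adding low-functioning survivors to that arm.
- **That mortality by arm will go unreported.** Deaths could still appear in the participant flow; the article does not say they will not, and its flowchart is not shown.

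**Conclusion.** The contradiction is certain and rests on the text alone: the death and early-withdrawal exclusions remove randomised patients, and intention-to-treat for all aims cannot be honoured alongside them. The exclusion in the Intervention group section belongs to the same conflict, as do refusal and amputation whenever they follow randomisation.

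The bias is a risk, not an established fact. It arises if exclusions differ between arms in rate or in type of patient, and nothing in the design prevents that. With no death or exclusion rates in the article, neither size nor direction can be fixed. The illustrative 1.2 to 4.3 points is roughly 9% to 33% of the planned 13 (1.2/13 and 4.3/13) and holds only under the one-arm assumptions above. A larger sample would restore precision but would not remove this bias.

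The point should be resolved before analysis because the rule determines who is in the primary comparison.

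**What to change.** Reconcile the Participants, Intervention group and Statistical analysis sections as follows.

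1. Limit exclusions to criteria that are checked before the envelope is opened. Remove death, withdrawal, and post-allocation refusal or amputation as reasons for leaving the study. Clarify or remove the activity-level exclusion in the Intervention group section.
2. Keep following patients who refuse, stop or withdraw from the exercises, and assess them at ICU discharge, unless they withdraw consent for their data.
3. Analyse all randomised patients by assigned arm.
4. State in advance how deaths enter the primary comparison: either a ranked composite with death as the worst result, or a survivors-only comparison declared and labelled as such. Use the other as a sensitivity analysis.
5. Report deaths and withdrawals by arm.

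The cost is amendment wording and a little more analysis. The choice in step 4 is a real trade-off. A ranked composite keeps every patient but changes the question to one about mortality and function together. Its power can fall well below 80% when deaths are similar in both arms (about 61% at 10% deaths and 51% at 15%, rates assumed), so the stated power would have to be restated if it becomes primary. A survivors-only comparison retains more power but remains open to selection by survival, which is why it needs its label and the deaths by arm beside it.

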### Details of the intervention and control

The study will consist of two groups: control and intervention. Patients will be randomized into groups using a computer program after evaluation of the inclusion criteria. Both groups will receive respiratory care according to the routine of the ICU and will receive physiotherapy twice daily. The ICU staffs a physiotherapist at all times. Patients in the intervention group will receive conventional physiotherapy in the morning and perform the research protocol in the afternoon period, thus receiving physiotherapy twice a day. Patients in the control group will also receive physiotherapy twice a day, performing conventional physiotherapy in both the morning and afternoon.

#### Control group

The control group will perform the conventional treatment offered by the unit physiotherapists. The unit physiotherapist will not have access to the protocol and equipment used, and the exercises that patients perform will be at the physiotherapist’s discretion. Conventional therapy consists of passive, active assisted, and active mobilization as well as bed positioning, bedside and armchair transfers, orthostatism, and ambulation; however, the type of therapy will not be defined in advance, but instead will be at the discretion of the attending physiotherapist and without a pre-established routine. No technological equipment will be used for this group, as these elements are not part of the normal service.

#### Intervention group

The intervention group will undergo a program of early and progressive mobilization (Fig. 1) created by the research team, based on data in the academic literature. As maintenance of functionality seems to depend primarily on the muscular and cardiorespiratory systems, the program is designed for rehabilitation focused on these systems. The protocol describes exercises, techniques, and apparatus for maintenance of muscle length, maintenance and gain of muscle strength, aerobic exercises, exercises aimed at reeducation of gait, and cognitive components.

**Fig. 1 Fig1:**
[figure not shown]
Progressive mobilization program

The patients will undergo the prescribed program therapy at the appropriate level for each patient, chosen based on the physiotherapist’s evaluation and evolving within the protocol as described below. The program should be started within 48 h of ICU admission. The patient will be included in the program throughout their stay in the ICU and will be assisted by a specific physiotherapist to apply only the prescribed protocol.

According to the program description (Fig. 1), the patients in the intervention group will have equipment and technologies for the therapy. These devices are a functional electrical stimulator (Fesmed II, Carci®, São Paulo, Brazil), dumbbells, shin guards, a Motomed Letto® active and passive cycle ergometer (RECK Company, Bremen, Germany), a fixed walker, a LiteGait 300MX-30® ambulatory device (Mobility Research, Tempe, AZ, USA), and a Wii Fit® video game with sitting and standing games (Nintendo®, Redmond, WA, USA).

If, during hospitalization, the patient evolves with criteria that indicate that any level of activity has been performed for more than 2 days, they will be excluded from the study.

The five levels of the early and progressive mobilization program (Fig. 1) are described below.

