From level II onwards, patients can advance by one level when they can perform all the exercises prescribed for that level. Therefore, at levels III, IV, and V in the early and progressive mobilization program, the patient must be able to perform all of the physical exercises and postural changes at their present level or they will remain at the same level for the following day. When patients can complete all of the activities, they advance to the next level on the following day.

Patients in both the control and intervention groups will be monitored throughout the therapy for hemodynamic and respiratory stability. Therapy will be discontinued if the RR is above 35 breaths/min, the MAP is below 60 mmHg or above 120 mmHg, the HR is below 60 bpm or above 140 bpm, or the patient experiences discomfort or unrelenting pain during the therapy.

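### An exclusion sentence in the intervention section, read literally, removes most treated patients after randomisation; it contradicts other sections and must be reconciled with them

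*Protocol article*

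**What the plan says.** All references are to the protocol article.

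- **Intervention group (text under Fig. 1).** A patient leaves the study if, during hospitalisation, "any level of activity has been performed for more than 2 days, they will be excluded from the study". The same text says: "The patient will be included in the program throughout their stay in the ICU". It also says: "The program should be started within 48 h of ICU admission".
- **Details of the intervention and control.** Programme sessions are daily: "Patients in the intervention group will receive conventional physiotherapy in the morning and perform the research protocol in the afternoon period".
- **Choice of activity level and criteria for progression.** Patients must manage everything at their present level "or they will remain at the same level for the following day". No limit is set on the number of days at a level.
- **Setting.** "The average stay in the ICU is 12 days". This is a figure for the whole unit, and no spread is given.
- **Participants.** The listed exclusions include patients "who refuse to carry out the proposed exercises or ask to withdraw less than 3 days after beginning the protocol", and also contraindication to movement, amputation and death before the final evaluation. The 2-day activity rule is not among them.
- **Patient assessment procedures.** All patients are to have the complete evaluation at ICU discharge or within 2 days of it.
- **Statistical analysis including sample size calculations.** All aims are to be analysed by intention to treat. The Barthel Index is powered for a difference of 13 points with SD 22 and 48 patients per group.

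**The concern.** The trigger is having performed activity for more than 2 days, which is what the programme sets out to deliver. A site that followed the sentence would discard patients because they were treated as planned. The sentence may have lost a negation, so that it was meant for patients who could not be mobilised for more than 2 days. No other section confirms that.

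Both senses select patients on something that happens after randomisation, so both conflict with intention to treat. The consequences differ. The literal sense would cost most of the intervention arm. The opposite sense would remove patients with a poor clinical course, and if only one arm lost them, the primary comparison would be biased in favour of the intervention.

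An analysis plan cannot repair this later if the discharge evaluation was never done on patients removed from the study.

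**Working it through.** **1. The plan's own sample size.** n per group = 2 × SD² × (1.96 + 0.84)² / difference² = 2 × 22² × 7.849 / 13² = 44.96, so 45 (46 with the t distribution). The plan has 48. This agrees closely enough with two-sided alpha 0.05 and 80% power to serve as the base. (Alpha is printed as 0.5, which would give 14 per group. That is a separate matter.) Power at 48 per group is 82.5% by the normal approximation.

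**2. Literal reading: share with more than 2 programme days.** With a mean stay of 12 days and a start by day 2, an average patient has about 12 − 2 = 10 programme days, five times the threshold. The stay distribution is not given, so shapes with mean 12 are assumed. The share is S(start + 2) / S(start), where S is the survival function of the stay and the start is day 0, 1 or 2. For the exponential it is exp(−2/12) = 0.846 at any start.

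| Assumed shape, mean 12 days | Share over 2 programme days |
|---|---|
| Exponential | 85% |
| Gamma, shape 2 | 90% to 96% |
| Gamma, shape 0.5 | 68% to 83% |
| Lognormal, sigma 0.6 | 94% to 99.6% |
| Lognormal, sigma 1.0 | 80% to 90% |
| Lognormal, sigma 1.3 | 74% to 77% |

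**3. Narrower reading: more than 2 days at one single level.** A patient starting at level III has three levels left, so at most 3 × 2 = 6 programme days can pass before some level exceeds 2 days. A patient starting at level I has at most 5 × 2 = 10. Under the same shapes, the share with more than 6 programme days is about 45% to 80%, and with more than 10 about 31% to 50%. These are minimum shares, because slower progression adds to them.

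**4. Power if the literal rule removed intervention patients only.** SE = 22 × √(1/n + 1/48), and power = Φ(13/SE − 1.96).

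| Removed from intervention arm | Left of 48 | SE | Power |
|---|---|---|---|
| 0% | 48 | 4.49 | 82.5% |
| 75% | 12 | 7.10 | 45% |
| 85% | 7 | 8.90 | 31% |
| 90% | 5 | 10.34 | 24% |

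**5. Opposite reading, intervention arm only, no true effect.** If a fraction p is removed on a variable with correlation r to poor outcome, the mean of those left rises by r × SD × φ(z_p) / (1 − p). The values of p and r are assumptions; the documents give neither.

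- p = 0.10: 22 × 0.1755 / 0.90 = 4.29 points at r = 1.0, and 2.14 at r = 0.5.
- p = 0.20: 22 × 0.2800 / 0.80 = 7.70 points at r = 1.0, and 3.85 at r = 0.5.
- Smaller inputs: p = 0.10 with r = 0.3 gives 4.29 × 0.3 = 1.3 points. p = 0.05 with r = 0.5 gives 0.5 × 22 × 0.1031 / 0.95 = 1.2 points.

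Simulated trials with 48 per group and a two-sided 5% t test gave false-positive rates of about 8% to 18% for p = 0.10 and 13% to 43% for p = 0.20, over r = 0.5 to 1.0. The two smaller settings stay near 5% to 6%.

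**6. Opposite reading, same fraction removed from both arms.** The mean spurious difference is about 0 in every setting, and at r = 0.5 the false-positive rate stays close to 5% (about 6%).

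**The case against.** The strongest reply is that this is a slip of language that no site would apply literally, since doing so would exclude patients for receiving the intervention. That is plausible. But the article nowhere states the intended rule, and the sentence is in the current operative text of a trial that is already recruiting.

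Three further objections stand in part or in full.

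- **One arm or two.** A reader might infer that the rule prunes the intervention arm alone, because it sits under that heading, speaks of activity levels, and has no counterpart in the control description. The documents do not establish this. The exclusion is from the study, the control section is only a short account of usual care, and Participants lists study-wide exclusions that include contraindication to movement and several events after entry. The 2 to 8 point bias is therefore conditional.
- **How many patients.** A reader might infer that the intervention arm would be emptied. The 12-day mean describes the whole unit, whereas enrolled patients are selected on prior independence and early stability, and their own stay is not given. Most patients is as far as the figures go.
- **Size of the inputs.** A correlation of 1.0 means that the rule removes exactly the worst outcomes, and the upper ends of the bias and error ranges come only from that case. Deaths are already excluded by a separate rule, so some of the sickest patients may be out in any case.

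Nothing in the article shows that any patient has actually been removed under this sentence.

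**Conclusion.** The sentence is wrong as written. It contradicts its own section, the progression rules, the discharge evaluation of all patients and the intention-to-treat statement, and it is missing from the exclusion list. That conclusion needs no assumption.

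The size does need assumptions. Read literally, the sentence would remove most intervention patients: about 68% to nearly 100% if the enrolled patients' mean stay is 12 days, or at least about 31% to 80% on the single-level reading. Read in the opposite sense, it is still a post-randomisation exclusion that breaks intention to treat. It would bias the Barthel comparison by about 2 to 8 points only if it falls on one arm and 10% to 20% are removed with correlation 0.5 to 1.0. The bias is smaller with smaller inputs, and about 0 on average if both arms are pruned equally. At the top of that range, 7.7 points is more than half of the 13-point target.

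**What to change.** Amend the sentence so that it states the intended trigger and whether it covers both arms. Reconcile it with Participants, with the statement in its own section that patients stay in the programme throughout, with the progression criteria, with Patient assessment procedures and with the intention-to-treat statement. Which trigger is clinically right is for the sponsor to say; no clinical or treatment-stopping rule is proposed here.

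Whatever the trigger, add that it does not remove a randomised patient from the ICU-discharge evaluation or from the analysis in the assigned arm. Report how many patients in each arm, if any, have already been removed under the sentence. Restore them to the analysis set and retrieve their outcomes where possible.

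The cost is a sentence or two in an amendment, plus outcome retrieval for any patients affected. Because recruitment is under way, discharge evaluations missed in the meantime may not be recoverable.
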